**Figure 1 fig1:**
[figure not shown]
Flowchart of the study process. HADS, hospital anxiety and depression scale; Gwet’s AC1, Gwet’s agreement coefficient 1.

### Study population

2.2

All patients with FGIDs presenting to Peking Union Medical College Hospital, a tertiary hospital in Beijing, China, will be assessed for eligibility during the appointment, starting from January 2025 and being estimated to be completed in December 2025.

#### Inclusion criteria

2.2.1

Age 18–80 years.The patients diagnosed with FGIDs during outpatient visits to the Department of Gastroenterology at Peking Union Medical College Hospital and who will provide consent for follow-up treatment and care. The study will primarily enroll patients who meet the Rome IV criteria (18) for functional dyspepsia, irritable bowel syndrome, functional constipation, and other FGIDs. Other FGIDs encompass chronic diarrhea, centrally mediated abdominal pain syndrome, functional esophageal disease, and functional anorectal disease.The patients must provide consent for the collection of facial video and completion of HADS psychological self-assessment.The patients must consent to undergo conventional treatment for FGIDs.The patients are able to sign the informed consent.

#### Exclusion criteria

2.2.2

The patients who fulfill any of the following criteria will be excluded:

Age under 18 years old or over 80 years old.The patients presenting with celiac disease, inflammatory bowel disease, or other organic gastrointestinal disorders are typically diagnosed based on evident structural abnormalities or pathological changes. This comprehensive evaluation includes a detailed medical history, thorough physical examination, and auxiliary diagnostic tests.The patients presenting with secondary gastrointestinal motility disorders due to primary diseases such as cholecystitis, pancreatitis, hyperthyroidism, diabetes, chronic renal insufficiency, and neurological diseases.The patients who are reluctant to seek medical treatment and attend regular follow-up appointments at our hospital.The patients are either pregnant or lactating.The patients with severe comorbidities that impact medication management, such as severe hepatic insufficiency, renal failure, and congestive heart failure. The exclusion of such patients is a precautionary measure to avoid potential adverse drug reactions and to maintain the efficacy and safety of the study’s intervention.The current medication regimen includes antipsychotics, spasmolytics, antidiarrheals, probiotics, antibiotics, and other pharmacological agents utilized for the management of abdominal pain, intestinal peristalsis disorders, and gastrointestinal motility disturbances.

#### Withdrawal criteria

2.2.3

If a participant withdraws from the study based on predefined withdrawal criteria, any data collected from that participant up to the point of withdrawal will be excluded from subsequent analyses. This approach ensures the integrity of the study results and maintains consistency in data analysis.

Subjective inclination towards study withdrawal due to various considerations subsequent to enrollment.The patients are unable to successfully complete the vibraimage technology process or undergo HADS psychological self-assessment in this study.

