#### The evaluation metric for the diagnostic test

2.6.1

Primary Outcome: Sensitivity and specificity of vibraimage technology compared to HADS as the gold standard.

Secondary Outcomes: Positive predictive value (PPV), negative predictive value (NPV), and overall accuracy of vibraimage technology.

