#### The assessment of patient prognosis and satisfaction

2.6.2

The patients will be divided into two groups according to HADS, that is with or without psychological disorder group. The patients in both groups will receive the conventional treatment, without any additional interventions beyond the standard care for FGIDs. The treatment effect questionnaire will be administered after 4 weeks. Overall improvement will be evaluated using a 5-point Likert scale (36), where patients will be prompted to complete the following statement: “How does my gastrointestinal condition compare to before I commenced treatment at the clinic?” The response options include: deteriorated, slightly deteriorated, unchanged, slightly improved, and significantly improved. The HADS and vibraimage technology will also be systematically evaluated.

Primary endpoint: the overall rate of improvement, specifically referring to the proportion of patients who achieved Likert scores greater than or equal to 4.

Secondary endpoint: HADS and vibraimage technology outcomes, along with the improvement degree of FGIDs symptom scores such as IBS-SSS, quality of life by SF-36 questionnaires, and the patients’ satisfaction with treatment.

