### Descriptive statistics

2.9

The consistency analysis is conducted based on Gwet’s Agreement Coefficient 1 (AC1, 38) to assess the concordance between vibraimage technology and HADS detection results, as well as to determine the optimal threshold for vibraimage technology. Specifically, a HADS-A score of 8 or higher indicates anxiety, while a HADS-D score of 8 or higher suggests depression (10).

The measurement data that conform to a normal distribution are represented by *x̄* ± *s*, while the ones that do not conform are represented by the median (interquartile range). The difference between the two groups of measurement data following a normal distribution is assessed using a student *t*-test, whereas the difference between the two groups of measurement data not following a normal distribution is assessed using Mann–Whitney U test. The difference between the two groups is evaluated using *χ*^2^ test. Oneway-ANOVA analysis is employed for group comparisons. Pearson correlation analysis is used for measurement data with a normal distribution, and Spearman correlation analysis is used for measurement data without a normal distribution.

In the process of conducting binary logistic regression analysis to determine whether patients with FGIDs are also affected by psychological disorders, we will continuously enhance the model’s goodness of fit by eliminating irrelevant independent variables. Subsequently, a diagnostic model with high diagnostic efficiency will be derived. Finally, a Receiver Operating Characteristic (ROC) curve will be constructed based on the performance of sensitivity and specificity at various thresholds. This analysis will aid in identifying the optimal diagnostic test threshold and in evaluating the accuracy, sensitivity, and specificity of the test.

Variables with a *p* value <0.05 are considered statistically significant. The statistical analysis will be conducted by a medically trained personnel who will remain blinded to the assignment of study groups. The data statistics in our study will be conducted using paper questionnaires. In the event of missing items, we will either discard the questionnaire or, if necessary, employ imputation techniques to fill in the missing values.

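### The withdrawal rule drops valid baseline data and unreported vibraimage failures, so both primary outcomes rest on a selected subset with a risk of bias of unknown size

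*Protocol article*

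**What the plan says.** Section 2.2.3 (Withdrawal criteria) states that on withdrawal "any data collected from that participant up to the point of withdrawal will be excluded from subsequent analyses". The reason given is: "This approach ensures the integrity of the study results and maintains consistency in data analysis".

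Two criteria trigger the rule. The first is the participant's own wish: "Subjective inclination towards study withdrawal due to various considerations subsequent to enrollment". The second is test failure: "The patients are unable to successfully complete the vibraimage technology process or undergo HADS psychological self-assessment in this study".

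Two primary outcomes are affected. Section 2.6.1 names "Sensitivity and specificity of vibraimage technology compared to HADS as the gold standard", and section 2.1 has both tests done simultaneously, before treatment. Section 2.6.2 names "the overall rate of improvement, specifically referring to the proportion of patients who achieved Likert scores greater than or equal to 4", with this timing: "The treatment effect questionnaire will be administered after 4 weeks".

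Section 2.7 allows for 10% attrition in each of its two sample size calculations, and section 3 lists dropouts and data loss as a limitation. Nowhere does the article return excluded patients to an analysis, say that failed recordings will be counted, or plan a sensitivity analysis for them.

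**The concern.** The rule does three separate things.

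1. **It discards usable accuracy data.** Sensitivity and specificity need only the baseline pair. A patient who withdraws before week 4 has already supplied it. The second criterion is not limited to baseline, and both tests are repeated after treatment. Read literally, a failed recording at week 4 could also remove a complete baseline pair.
2. **It hides index-test failures.** The study aims to judge vibraimage as a screening tool in consecutive outpatients. A patient who cannot be recorded is one the tool cannot screen. Removing such patients gives accuracy among recordable patients only, and the reader is not told how many could not be recorded.
3. **It restricts the improvement rate to those who stay.** Staying may depend on psychological status, on response, or on both. The Introduction itself says that comorbid patients respond poorly to conventional treatment.

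The stated justification therefore does not hold: exclusion after enrolment, for reasons that may be related to the result, puts integrity at risk.

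**Working it through.** **Inputs (section 2.7).** Assumed sensitivity 0.80; prevalence 0.50; margin 0.07; α 0.05 (taken as two-sided); attrition 10%; improvement rate P1 = 0.57; P2 at half of P1 = 0.285. The article gives no failure rate, no split of attrition by reason and no assumed specificity. The exclusion share *f* below is therefore an assumption, set at 10% to match the attrition figure and varied from 5% to 15%.

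**The plan's own figure.** HADS-positive patients needed: 1.96² × 0.80 × 0.20 / 0.07² = 125.4. Divided by 0.50 this is 250.9, so 251 is reproduced. 251 × 1.10 = 276.1, which matches 276.

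**Precision after exclusion.** 276 × 0.50 × 0.90 = 124.2 HADS-positive patients remain. Half-width = 1.96 × √(0.16 / 124.2) = 0.0703, against 0.07 planned. Precision is nearly kept, so the problem is selection, and a larger sample would not cure it.

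**Bounds on sensitivity.** Overall value = c(1 − f) + x·f, where c is the completer value and x the unknown value among the excluded. With c = 0.80:

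| f (assumed) | x = 0 | x = 0.4 | x = 0.8 | x = 1 |
|---|---|---|---|---|
| 5% | 0.76 | 0.78 | 0.80 | 0.81 |
| 10% | 0.72 | 0.76 | 0.80 | 0.82 |
| 15% | 0.68 | 0.74 | 0.80 | 0.83 |

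At 10%, completer minus overall runs from +8 to −2 points, and is zero if exclusion is unrelated to accuracy. The same formula applies to specificity.

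**Bounds on the improvement rate, f = 10%.**
- Completer 57%: 0.57 × 0.90 = 51.3% if no excluded patient improved; 51.3% + 10% = 61.3% if all did.
- Completer 28.5%: 0.285 × 0.90 = 25.65%; with all improved, 35.65%.

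**Group difference, excluded patients counted as not improved** (completer difference 28.5 points; withdrawal shares without/with psychological disorder assumed):
- 10%/10%: 51.3 − 25.65 = 25.7 points.
- 5%/15%: 0.57 × 0.95 − 0.285 × 0.85 = 29.9 points.
- 0%/20%: 57 − 0.285 × 0.80 = 34.2 points.

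The contrast can move either way.

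**The case against.** **Direction.** A reader might infer that the reported accuracy and improvement rates will be biased upward. The documents do not show this. They give no failure rate and no link between failure or withdrawal and accuracy or improvement. Withdrawal that depends only on HADS class would leave sensitivity and specificity unbiased. Patients may leave because they have recovered as well as because they have not. What stands is that upward bias is the more likely direction for accuracy, because a patient who is hard to record is plausibly also hard to classify, and an unrecordable patient is not detected in practice.

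**Scoring failures as misses.** The 72% figure follows from a scoring convention and is not an estimate of bias. That is correct, and it is why it is shown only as one end of a range.

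**Number of patients.** A reader might infer that 276 × 0.10, about 28 patients, will be lost through this rule. That treats all attrition as formal withdrawal. Section 2.2.3 covers only its two listed criteria, and a patient who merely misses week 4 is not clearly included. The follow-up denominators are not visible either: section 2.7 needs 98 patients for that part and refers to a figure that is not shown.

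**Unavoidable exclusions.** Patients without a HADS result have no reference standard and no group, so they cannot enter sensitivity or specificity under any rule. This part of the second criterion is not open to criticism on the accuracy outcome.

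**Missing items.** It is tempting to add the section 2.9 provision on incomplete questionnaires. It does not belong here: it allows imputation, its detail is commonly left to an analysis plan, and the primary improvement endpoint is a single statement.

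None of this rescues the rule. It is stated outright, so an analysis plan that kept these patients would contradict the protocol.

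**Conclusion.** The rule is wrong as written. It removes complete baseline pairs from the accuracy analysis, takes index-test failures out of the denominators unreported, and leaves withdrawers out of the 4-week improvement rate. Both primary outcomes are therefore computed on a selected subset.

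The consequence is a risk of bias, probably upward for accuracy, with no determined direction for the improvement rates or the group contrast. The bounds of 72% to 82% for sensitivity and 51.3% to 61.3% for improvement rest on an assumed 10% exclusion and on completer values set equal to the planning values. They show what the plan would leave unknown and do not predict the result. For withdrawers who already have a baseline pair, the accuracy uncertainty is avoidable, because the data are in hand.

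**What to change.** 1. Delete the exclusion rule in section 2.2.3. Keep data collected before withdrawal unless the participant withdraws consent for their use.
2. Analyse accuracy in all patients with baseline HADS and vibraimage results, regardless of later follow-up.
3. Report the number and share of failed recordings by HADS class, with a sensitivity analysis that counts them as not correctly classified.
4. Report the 4-week improvement rate for all patients entered into follow-up, using a pre-specified missing-data method with best-case and worst-case bounds. Step 1 alone is not enough here, because a patient who leaves before week 4 has no Likert answer.

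Whether failures count as misclassified in the main or a supporting analysis, and which missing-data method is used, are choices for the team, provided they are fixed in advance.

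The cost is revised wording and a few extra analyses, with no added patients or procedures. The reported accuracy may be slightly less favourable.

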### Baseline data collection

2.3

Vibraimage data specialist is responsible for collecting and analyzing the patient’s vibraimage technology data, while the HADS assessment specialist will handle the general information collection and analysis of the patient’s HADS self-rating data. Both specialists are unaware of each other’s datasets. The physicians will solely administer conventional treatments based on FGIDs diagnostic criteria, without any knowledge of the results obtained from vibraimage technology or HADS questionnaires.

The following information will be collected: demographic data (age, gender, height, weight), marital and childbearing status, occupation and education level; disease-related details including course of illness, diagnosis and classification of FGIDs, treatment process, and dietary habits. The FGIDs symptoms will be generally assessed by5-point Likert score. Patients diagnosed with irritable bowel syndrome will be evaluated based on their IBS Severity Score (IBS-SSS) (19); patients with functional dyspepsia, as well as those with constipation, will be assessed using the relevant symptom scores (20, 21); while patients with other functional disorders will be evaluated through the Gastrointestinal Symptom Severity Index (GISSI) (22). Baseline questionnaires will be administered to assess anxiety and depression levels using the Hospital Anxiety and Depression Scale (HADS), and general health-related quality of life using the Health Status Questionnaire (SF-36) (23).

### The principles and implementation of vibraimage technology

2.4

The vibraimage technology in this study is supported by Beijing Sinovoice Technology Co., Ltd.

The imaging principle, vibration extraction method, and vibration visualization method involved in the vibration measurement method based on machine vision have been thoroughly investigated (24–27). Video image amplification technology is utilized to extract and amplify minute vibrations in the video, while vibration visualization is achieved through video reconstruction for enhanced amplification of video images. The primary focus of this research is to directly extract structural vibration signals by analyzing local phase changes in the image. Spatial filtering (24) is applied to calculate local phase and amplitude information for each pixel in every frame of the video image. Phase information indirectly represents subtle motion within the video, which can be amplified by processing this phase information using Fourier transform’s time-shift property (25) that transforms position information into frequency domain phase information. By calculating phase contour videos at different scales, the phase difference signal for each pixel position within these contour videos can be extracted as a vibration signal. The averaged frequency spectrum of all phase difference signals serves as the frequency spectrum for the vibration signal, leveraging correlations between image frequency domain information and motion (26). Furthermore, denoising techniques (27) are employed on local amplitudes to enhance measurement accuracy.

Human micromovements, also known as vibrations, can be measured using standard digital, network or television cameras and image processing technologies. These movements are closely linked to the human vestibulo-emotional reflexes (VER) and can reflect emotional states and personality traits (28). By detecting three-dimensional (3D) head and neck movements over several video frames, fluctuations in emotions can be identified (29). As depicted in Figure 2, each pixel of a video image represents a vibration parameter such as frequency or amplitude. The visualization of these parameters is called an external vibration image (30) which resembles a vibratory halo around the person’s head. Generally, the color of this image corresponds to the vibration frequency while its size reflects the amplitude. This mapping of micro-changes to individuals’ psychological states allows for the development of a video-based psychological assessment method. Currently, this technology can give assessment reports of patients’ psychological status, for example, whether they have anxiety or depression status. The primary application of this technology lies in the realm of public safety, encompassing lie detection and human-computer interaction systems (31–34). Furthermore, it holds significant potential for clinical disease diagnosis, particularly in cases related to depression (35). The patients diagnosed with FGIDs will be instructed to assume an upright position, facing the camera, for approximately three minutes of video recording.

**Figure 2 fig2:**
[figure not shown]
Human micro-vibration images.

### Conventional treatment

2.5

Patients enrolled in the study with FGIDs will receive conventional specialty care in gastroenterology. The clinician needs to determine which symptom features are dominant, and which treatment (s) are most likely to lead to improvement. Certain patients may find simple, cost-effective interventions such as laxatives or anti-diarrheal medicine (2). Treatment principles for patients with the same subtype of FGIDs are consistent, but actual treatment plans may vary slightly based on individual patient circumstances. The conventional treatment in this study does not encompass the utilization of psychotherapeutic drugs and psychotherapy.

### Outcome measures

2.6

#### The evaluation metric for the diagnostic test

2.6.1

Primary Outcome: Sensitivity and specificity of vibraimage technology compared to HADS as the gold standard.

Secondary Outcomes: Positive predictive value (PPV), negative predictive value (NPV), and overall accuracy of vibraimage technology.

#### The assessment of patient prognosis and satisfaction

2.6.2

The patients will be divided into two groups according to HADS, that is with or without psychological disorder group. The patients in both groups will receive the conventional treatment, without any additional interventions beyond the standard care for FGIDs. The treatment effect questionnaire will be administered after 4 weeks. Overall improvement will be evaluated using a 5-point Likert scale (36), where patients will be prompted to complete the following statement: “How does my gastrointestinal condition compare to before I commenced treatment at the clinic?” The response options include: deteriorated, slightly deteriorated, unchanged, slightly improved, and significantly improved. The HADS and vibraimage technology will also be systematically evaluated.

Primary endpoint: the overall rate of improvement, specifically referring to the proportion of patients who achieved Likert scores greater than or equal to 4.

Secondary endpoint: HADS and vibraimage technology outcomes, along with the improvement degree of FGIDs symptom scores such as IBS-SSS, quality of life by SF-36 questionnaires, and the patients’ satisfaction with treatment.

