## Introduction

1

Functional gastrointestinal disorders (FGIDs), also known as disorders of gut–brain interaction (DGBI), manifest as a variety of gastrointestinal symptoms such as nausea, vomiting, abdominal pain, bloating, diarrhea, and constipation, which have been excluded organic lesions through objective examinations. Functional dyspepsia, irritable bowel syndrome and functional constipation are the most common FGIDs in clinical practice (1). The pathophysiological mechanisms of FGIDs are complex, involving abnormalities in gut–brain interaction, dysbiosis of intestinal flora, alterations in mucosal immune function, visceral hypersensitivity and gastrointestinal dysmotility (2). A large-scale epidemiological study showed over 40% of individuals worldwide suffered from FGIDs, which significantly impacting the quality of life (3). Recent studies have indicated that approximately 50% of FGIDs patients also experience comorbid anxiety and depression (4–6), which leads to a poor response to conventional treatments. As a result, these patients often require the use of neuromodulators in conjunction with cognitive-behavioral therapy to achieve clinical relief. In accordance with the Rome Foundation’s definitional guidelines, neuromodulators are divided into central and peripheral types, with central agents such as antidepressants, antipsychotics, and buspirone, and peripheral agents including serotonergic drugs, chloride channel modulators, and α2δ (delta) ligands (7). Most gastrointestinal specialists may lack a background in psychology. And up to now, there are no rapid and effective screening tools for identifying FGIDs patients comorbid with psychological disorders, resulting to recurrent visits, cost issues and substantial healthcare resource utilization (3, 8, 9).

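### The 4-week global improvement item is anchored to the start of treatment at the clinic rather than to study entry, so for previously treated patients it can include change from before enrolment

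*Protocol article*

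**What the plan says.** Section 2.6.2 defines the primary endpoint of the treatment part as "the proportion of patients who achieved Likert scores greater than or equal to 4". On timing it says: "The treatment effect questionnaire will be administered after 4 weeks". Patients complete an item worded "How does my gastrointestinal condition compare to before I commenced treatment at the clinic", with five answers from deteriorated to significantly improved. Numbered in the listed order, scores of 4 and 5 are the two improved categories. The item names neither enrolment nor the baseline visit nor the 4-week interval.

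On who can enter:

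- Section 2.2 (Study population): "All patients with FGIDs presenting to Peking Union Medical College Hospital, a tertiary hospital in Beijing, China, will be assessed for eligibility".
- Section 2.2.1 (Inclusion criteria): "The patients diagnosed with FGIDs during outpatient visits to the Department of Gastroenterology". It sets no condition that this be a first visit or that the patient be untreated.
- Section 2.2.2 (Exclusion criteria) excludes on present drug use: "The current medication regimen includes antipsychotics, spasmolytics, antidiarrheals, probiotics, antibiotics, and other pharmacological agents" for pain and motility complaints. It gives no washout and no exclusion for past treatment.

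Sections 2.1 and 2.3 place the HADS grouping, the disease-specific symptom scores and the SF-36 at study baseline. Section 2.3 also records course of illness and treatment history.

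**The concern.** The treatment part is meant to compare how patients with and without psychological comorbidity fare over 4 weeks of the same conventional care. The symptom scores and SF-36 are measured at study baseline and again afterwards, so their change covers that interval. The primary endpoint is a single retrospective rating, and each patient's own history at the clinic sets its starting point.

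If a patient was treated at the clinic some time ago, stopped, and then enrolled, a literal answer looks back to before that earlier episode. The rating then mixes earlier change with the 4-week change. Later analysis cannot separate the two, because there is only one number per patient. At stake is whether the improvement rate measures 4-week response in everyone, or only in those new to the clinic.

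**Working it through.** **Does the anchor equal baseline?** This follows from the text alone.

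- Treatment at the clinic starts at enrolment: the anchor equals baseline, and nothing is wrong.
- Treated at the clinic before and still on a listed drug: excluded by section 2.2.2, so the question does not arise.
- Treated at the clinic before and now off the listed drugs: eligible under sections 2.2 to 2.2.2. Read literally, the anchor lies before enrolment.

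Only the third kind of patient is affected. The protocol does not say how many there will be.

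**The plan's own figure (section 2.7).** Inputs: improvement rate 57% without psychological disorder; half of that, 28.5%, with it; 1:1 allocation; alpha 0.05 (taken as two-sided); power 0.80; 10% loss. With the unpooled normal approximation:

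n per group = (1.960 + 0.842)² × (0.57 × 0.43 + 0.285 × 0.715) / (0.57 − 0.285)² = 7.849 × 0.4489 / 0.0812 = 43.4, rounded up to 44.

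Total 88, and 88 / 0.90 = 97.8, rounded up to 98. The stated 98 is reproduced. The anchor problem changes what is measured, not this calculation, so no corrected sample size follows.

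**Illustration of size. All shares are assumptions; none is in the protocol.** Let r be the share of previously treated patients, equal in both groups. Let g be the fraction of those who did not improve over the 4 weeks but still rate themselves better than before their first treatment at the clinic.

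Observed rate = p + r × g × (1 − p)

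With r = 0.20 and g = 0.20:

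- HADS-negative: 0.57 + 0.04 × 0.43 = 0.5872
- HADS-positive: 0.285 + 0.04 × 0.715 = 0.3136
- Difference: 0.2736, which is 1.1 points below the planned 28.5

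With equal shares the difference is 0.285 × (1 − r × g), which gives the range:

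| r | g | Difference (points) | Power at 44 per group |
|---|---|---|---|
| 0 | any | 28.5 | 0.78 |
| 0.10 | 0.10 | 28.2 | 0.77 |
| 0.20 | 0.20 | 27.4 | 0.74 |
| 0.30 | 0.20 | 26.8 | 0.72 |
| 0.50 | 0.30 | 24.2 | 0.63 |

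Power uses the pooled formula, which is why the first row is 0.78 and not 0.80. It applies only if 44 per group are evaluable.

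**Direction.** Suppose the shares differ: 50% of HADS-positive and 20% of HADS-negative patients previously treated.

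- Earlier improvement carried forward (g = 0.20): 0.285 + 0.50 × 0.20 × 0.715 = 0.3565 against 0.5872. The difference is 23.1 points, smaller than planned.
- The opposite case, where 20% of previously treated patients who did improve over the 4 weeks still feel no better than before their first treatment: 0.285 × (1 − 0.50 × 0.20) = 0.2565 against 0.57 × (1 − 0.20 × 0.20) = 0.5472. The difference is 29.1 points, larger than planned.

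The sign therefore depends on assumptions that the protocol cannot settle.

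**The case against.** The strongest reply is that the item has a natural reading that matches baseline. Patients consent to conventional treatment, both groups then receive it, and the questionnaire follows 4 weeks later. In that sequence, treatment at the clinic means the study's treatment. Section 2.8 also has trained doctors helping patients with questionnaires, so they could clarify the point. This reading is reasonable, but the words patients see do not enforce it, and the protocol does not say that the doctors will explain the reference point.

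Second, the exclusion of patients on the listed drugs probably removes many returning patients. That limits the size of the problem. It does not close the gap, because past treatment is not an exclusion.

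Third, the symptom scores and SF-36 are anchored at baseline and give a check on the global rating. That is true, but they are secondary and do not repair the primary endpoint.

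Fourth, the source scale and the questionnaire itself are not shown, so further instructions to patients may exist. That stands as a caveat.

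A reader might go further and infer that the bias distorts the comparison between groups, because the Introduction says that the lack of screening tools leaves comorbid patients "resulting to recurrent visits, cost issues and substantial healthcare resource utilization". The text does not support that step. It gives no rate, makes no comparison with patients without comorbidity, and does not say that the visits are to this clinic. Frequent attenders may also be more likely to be on an excluded drug. The same section says comorbid patients respond poorly to conventional treatment, which would leave them less earlier improvement to carry forward.

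**Conclusion.** The point holds as a flaw in the wording of the primary endpoint item. The anchor is not tied to enrolment, the criteria admit some patients for whom the two dates differ, and for them the rating can include change from before the study. It cannot be said that it does so, or how often.

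The documents establish no size, no direction and no difference between HADS groups. With equal shares of 20% and a 20% misreport, the difference moves by 1.1 points; with no previously treated patients it does not move at all. A loss of about 5 points (28.5 to 23.1) appears only if the shares are assumed to be very unequal, and should not be presented as an expected effect. The correction is still worth making because it concerns a primary endpoint, is cheap, and cannot be replaced by analysis afterwards.

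**What to change.** Reword the item in section 2.6.2 so that it refers to the study baseline, for example: *How is my gastrointestinal condition now, compared with the day I entered this study, 4 weeks ago?* The five answers and the cut-off of 4 stay as they are.

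The cost is one changed sentence on the paper questionnaire. It needs no extra visit and no extra patients. The downside is wording slightly different from the cited source scale, which should be acknowledged when results are compared with studies that used it.

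No new baseline field is needed. Earlier treatment at the clinic can be taken from the treatment history already collected under section 2.3, provided that the entry shows whether that treatment was given at this clinic.
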